### Participants

The following inclusion criteria will be used to select eligible patients for participation in the study:

• The patient is acutely admitted to the surgical ward with a hip fracture during the research period;

• The patient is not admitted with polytrauma;

• The hip fracture is not a pathological fracture;

• The patient is 65 years of age or older;

• The patient will be operated on the hip fracture;

• The patient does not participate in an interfering study;

• The patient is in a good cognitive condition to fully understand the information about the study and to give Informed Consent.

Patients will be recruited as quickly as possible after admission to the hospital. The patients will be included by the nurses working in de wards, this process will be closely monitored by the researchers. When a patient is eligible for participation the study will be explained to them and Informed Consent will be asked. If the inclusion by the nurses does not work out as intended, the researchers will have to take over this part of the data collection.

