#### Method

The incidence of complications and AEs will be measured within the care chain and especially during the hospital admission of elderly hip fracture patients. In this study we look at the care chain from the moment that the patient is brought into the emergency department until six months after discharge from the hospital. Therefore the patients' hospital record will be studied in retrospect by an experienced surgeon. For the baseline measurement patient records of hip fracture patients acutely admitted in 2007, the year previous to the start of the intervention study, will be reviewed using a structured review form. In each hospital all surgical and orthopaedic admissions of patients with a hip fracture of 65 years or older will be selected. Of these selected index admissions the medical, nursing and, if existing, the outpatient records will be collected, the X-rays made during the admission will also be available. Records of patients with a pathological fracture, polytrauma or elective admission will be excluded. The main outcome variables in this part of the study are: rate of complications, adverse events, near misses and information transfer between care providers.

The patient records will be reviewed by a team of eight experienced reviewers. The selection criteria for the reviewers are:

• At least ten years post graduate clinical (surgical) experience;

• Surgical experience with hip fractures;

• Good reputation among colleagues;

• No longer than 8 years retired at the start of the study;

• Experience or affinity with analysis of incidents, complaints and errors.

Most of the reviewers have participated in a previous record review study [39] and therefore are already familiar with this type of research, terminology and methodology. Nevertheless, they will all follow a half-day training led by the research team and one experienced reviewer. During this training, the definitions, study protocol, adjusted review form and examples of AEs will be discussed. The reviewers will also receive a review manual. They will be compensated for their review activities at an hourly rate for expenses. During the review process the reviewers can ask advice from a general internist about accepted clinical practice in the specialty of internal medicine.

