### General data collection and follow up

After receiving informed consent a questionnaire will be filled out with patient characteristics and the pre-fracture status of the patient. Information about the status before the fracture will be gathered using the 10-item modified Barthel Index for ADL-functioning [42], the Parker and Palmer pre-fracture mobility score [43], the Short Nutritional Assessment Questionnaire [44] and the Delirium Observation Screening Scale [45]. In addition, information will be gathered about the home situation before admission. Before discharge, the questionnaire will be completed with information about the occurrence of pressure wounds, delirium, urinary tract infections, wound infections, falls during admission and possible risk factors after discharge for these complications.

All included patients will be followed for a period of six months after discharge. During this period two interviews by telephone will be held with all included patients, two weeks and six months after discharge. During these interviews patients will be asked some multiple choice questions about their current residence, physical functioning, use of health care, the occurrence of unexpected events and some open end questions about their experiences during the whole care process. In addition to these interviews, the retrospective patient record review study will be conducted to review the patient record up to six months after discharge. The methods of this record review study will be identical to the baseline measurement described earlier. Again, the reviewers will look for complications, adverse events, the quality of record keeping and written information for the transfers of the patient between the different hospital wards. This second record review study will be used to assess the effect of the complete intervention programme on the possible reduction in complications and adverse events.

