The study also has some limitations. First, although the results of previous studies showed that the instruments used in retrospective record review studies are sensitive for identifying adverse events [46,47], there are some important factors that have to be considered. The retrospective patient record review method relies exclusively on the information available in the hospital patient record, this can be insufficient for adverse event determination [13,48]. Also, adverse events revealed after discharge are only found if they result in a readmission or if it is recorded in the outpatient record of the patient. The hospital record is not always complete with the risk of missing important information. A general possible weakness in retrospective review studies is hindsight bias [49]. Knowing the outcome and its severity may influence judgement of causation and preventability. A second limitation of the study is that elderly hip fracture patients suffering from dementia cannot be included into the study due to practical and ethical reasons, which may lead to an underestimation of the experienced problems and therefore the possible effects of the interventions. Some other issues that might influence the outcomes in this trial are the randomisation process, the blinding of patients and the possible effect of the presence of the researcher in the intervention wards. It was mentioned before that randomisation will be on patient level. It is possible that two patients in the same room receive different interventions and expose each other to the interventions. Another possible source of bias is that patients cannot be blinded, they are automatically aware of the intervention group that they will be in as they immediately receive the interventions after inclusion. A third issue is the presence of the researchers on the wards on a regular basis for the observations. Once a month the morning rounds will be observed to assess the effectiveness of the SBAR communication tool, this in itself can increase the use of the tool.

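### The 2007 baseline covers patients whom the trial excludes, so the planned comparison of complications with that baseline mixes any programme effect with a change in case mix

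*Protocol article*

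**What the plan says.** **Baseline sample (Protocol article, Baseline measurement, Method).** The 2007 record review is broad: "In each hospital all surgical and orthopaedic admissions of patients with a hip fracture of 65 years or older will be selected". Its exclusions are short: "Records of patients with a pathological fracture, polytrauma or elective admission will be excluded". Nothing there concerns cognition, operation or consent.

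**Trial sample (Participants).** Three criteria go further: "The patient is acutely admitted to the surgical ward with a hip fracture during the research period"; "The patient will be operated on the hip fracture"; and "The patient is in a good cognitive condition to fully understand the information about the study and to give Informed Consent". Patients in an interfering study are also left out. The section on strengths and limitations confirms the consequence for one group: "elderly hip fracture patients suffering from dementia cannot be included into the study due to practical and ethical reasons".

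**Use of the two reviews.** The aim of the baseline measurement describes it as the point from which the intervention effects are to be evaluated. The evaluation paragraph for Intervention B (the patient safety card) says outright that the complications and adverse events found in the second review will be compared with the baseline. The section on general data collection and follow-up says the second review will be "used to assess the effect of the complete intervention programme on the possible reduction in complications and adverse events". That section states that the review methods will be the same as at baseline; it does not say that the patients will be of the same kind.

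**The concern.** A before-after comparison can be read as an effect only if the two samples are of the same kind apart from the intervention. Here the after-sample is selected by criteria that the before-sample does not have to meet. If the patients dropped between the two reviews have more complications than those kept, the rate falls with no change in care.

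This matters because the SBAR tool is given to every patient in the intervention wards and, by the Randomisation section, cannot be randomised by patient. Randomisation therefore cannot isolate the effect of SBAR or of the complete programme. For that, the plan has the comparison with 2007 and the comparison with one separate, non-randomised control hospital. A case-mix artefact in the first removes one of only two sources of evidence.

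**Working it through.** **Step 1. Set the two populations side by side.**

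| Feature | 2007 baseline (Method) | Trial (Participants) |
|---|---|---|
| Age 65 or over | yes | yes |
| Pathological fracture, polytrauma, elective admission | excluded | excluded |
| Ward | surgical and orthopaedic | surgical ward only |
| Operation | not required | required |
| Good cognition | not required | required |
| Consent; no interfering study | not required | required |

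The last four rows differ. The first three of these can be checked at least partly from records; consent cannot.

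**Step 2. The benchmark.** The Power calculation section plans for an absolute reduction of 5 points in complication risk, SD 10%, alpha 0.05, power 80%, giving 64 per group.

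- Normal approximation, two-sided: n = 2 × (1.960 + 0.842)² × 10² / 5² = 62.8, so 63.
- Two-sample t-test: 63.8, so 64, which reproduces the stated figure.
- 64 / 0.80 = 80, so the recruitment aim corresponds to 20% drop-out.

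This calculation sizes the concurrent groups, not a comparison with 2007. The 5 points serve below only as a yardstick for the effect hoped for.

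**Step 3. The artefact under no effect.** Let p be the complication rate in trial-eligible patients, s the share of baseline records that fail the trial criteria, and d the complication rate in those records minus p. Assume also that eligible 2007 patients and trial patients share the same p.

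- Baseline rate = (1 − s)p + s(p + d) = p + s·d
- Trial rate = p
- Apparent reduction = s·d

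**Step 4. Numbers.** The document gives neither s nor d, nor any complication rate by dementia, operation or ward. Both are assumptions. Apparent reduction in percentage points:

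| s | d = −10 | d = 0 | d = 10 | d = 20 |
|---|---|---|---|---|
| 20% | −2 | 0 | 2 | 4 |
| 30% | −3 | 0 | 3 | 6 |
| 40% | −4 | 0 | 4 | 8 |

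A negative entry is a spurious increase. To produce the full 5 points with no true effect, d must be 5/0.20 = 25 points at s = 20%, 5/0.30 = 16.7 at 30%, or 5/0.40 = 12.5 at 40%.

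**Step 5. Effect on a test (illustration).** Assume 400 baseline records, 320 trial records (four intervention groups of 80), a trial rate of 40% and no true effect. With a two-sided 5% test of two proportions, the chance of a significant reduction is 2.5% with no artefact, about 8% with 2 points, 27% with 5 points and 57% with 8 points.

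**Step 6. Direction.** For dementia, the limitations section says that leaving these patients out is something "which may lead to an underestimation of the experienced problems and therefore the possible effects of the interventions". Its first half implies fewer recorded problems in the trial sample. Against a baseline that still contains dementia, that lowers the after-rate and makes a reduction look larger. The section draws only the opposite consequence, that effects may be understated, and does not consider the unrestricted baseline. For non-operated and orthopaedic patients the document states no direction. Non-operated patients, for example, cannot have operative complications.

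**The case against.** **The 2007 comparison is not the main effect comparison.** The Study design section compares the interventions with usual care, and the power calculation sizes concurrent groups. The sentence about assessing the complete programme names no comparator and could mean the concurrent control group; the one explicit sentence about comparing with baseline sits under the card. This stands in part. The randomised card and leaflet contrasts and the concurrent control-hospital contrast do not use 2007 records and are untouched. But the explicit sentence is there, and the baseline section gives the 2007 data a role in evaluating effects.

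**The direction is not settled.** A reader might infer that the comparison is bound to show a reduction even if nothing worked. The document does not support that. It speaks to direction only for dementia, and then with the word may. Other influences could act the other way: complications are actively noted before discharge in trial patients, and nurses carry a card on complete record keeping, so more events might reach the trial records. This stands, and it limits the claim to what could happen, and for dementia probably would.

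**Correction for differences is already planned.** The Data analysis section promises to compare patient characteristics across groups and correct if necessary. This does not answer the point. Adjustment cannot stand in for patient types that are absent from one sample by design; that needs restriction.

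**The choice of subset belongs in an analysis plan.** In part. However, the sampling frame is fixed in this article and the 2007 records are abstracted onto a paper form. If operation, ward and cognition are not captured there, a later plan cannot restrict the sample without reopening the records.

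**A broad baseline is right for research question 1.** Agreed; the fix leaves that use alone.

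**Conclusion.** The concern holds in a limited form. The mismatch in eligibility and the intended comparison are both in the text, and together they give a confounded before-after contrast. It could show a spurious reduction. Through the exclusion of dementia it probably would, on the document's own expectation that fewer problems are seen without these patients. For non-operated and orthopaedic patients no direction can be given.

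The size is not derivable from the document. The range of 2 to 8 points rests wholly on an assumed 20-40% share and 10-20 point excess; it reaches the planned 5 points only towards its upper end, and it vanishes or reverses if the excess is zero or negative. It should not be read as an estimate. Nor does the point show that the trial as a whole is biased, since the randomised and concurrent contrasts do not draw on the 2007 records. This is something that should be fixed, because a fall from baseline could not otherwise be attributed to the programme.

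**What to change.** 1. On the review form, record for each 2007 record whether the patient was operated on, which ward admitted the patient, and whether dementia or cognitive impairment is documented.
2. For the before-after comparison, use only 2007 records that meet these record-checkable trial criteria: operated, surgical ward, no documented dementia or cognitive impairment. With complete recording this sets s, and so the case-mix term s·d, to zero for these criteria.
3. Where 2007 records from the control hospital are available, set the change in the intervention hospitals against the change there.
4. Keep the full 2007 sample for research question 1, where the broad population is the right one.
5. State that selection by consent remains and cannot be removed from records, and that undocumented cognitive impairment may leave some residual mismatch.

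The cost is a few fields on the form, one subset analysis, and fewer baseline records in the comparison, hence a less precise baseline rate.

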### Intervention study

Within the intervention study three different interventions will be implemented in the surgical wards as described in the study design. The three interventions have in common that they all focus on information transfer and communication within the care chain for elderly hip fracture patients. The SBAR focuses on information transfer and communication between care professionals within the ward. The patient safety card is aimed at providing a complete picture of the current situation from patient to care provider. The information leaflet is aimed at providing useful information to the patient after discharge. In the text below each intervention will be described in more detail.

#### Intervention A: Implementing the SBAR communication tool (Research question 2a)

##### Aim

To improve communication among care providers, and for nurses to provide timely and accurate information during contacts with the physician and in the record keeping.

##### Background

Previous studies have shown that a model of structured communication can improve clinical communication [22,24]. The structured communication tool that will be used in the current study is SBAR. SBAR stands for *Situation, Background, Assessment and Recommendation *and is designed to structure and improve communication between care providers, and to provide timely and accurate information. The tool describes the most relevant points that can be discussed about a patient and how to effectively communicate them during various types of contact moments between care providers. It was developed and tested in the United States and proved to be useful there [24]. SBAR can be implemented in several ways, for instance using cards, posters near the telephones in the ward, hand-off forms and so forth to create awareness and stimulate nurses and clinicians to actively use the tool in handoff or clinical communication moments.

##### Implementation

For this study the original SBAR-tool will be translated and adapted in consultation with the participating wards to ensure that the relevant topics are present. These topics will be printed onto a pocketsize, laminated card that the nurses can keep with them during their shift. This card can be used during two different communication moments between care providers. On one side of the card there will be a description of the relevant items to discuss during the morning rounds or a telephone consult between the nurse and the physician about the condition of the patient. This side of the SBAR tool is shown in Table 2. On the other side will be a description of the relevant topics for a structured and complete record keeping. The SBAR-tool will be explained, discussed and handed over to the nurses during a meeting to announce and explain the study. The card will be accompanied by an example of a paper case how to use the SBAR-tool. Nurses will be asked to keep the card with them during their shift so that they have easy access to it and to use the card when consulting a physician or during the morning rounds. Since the SBAR-tool will be given to all nurses in the intervention wards it will apply to all hip fracture patients that are admitted during the research period.

**Table 2 T2:** Description of the SBAR communication tool

	Identify yourself (name, function). Do you have the information below available?
**S**	**Situation**

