## Methods/Design

### Study design

This RCT is set up as a multi-centre intervention study in which hip fracture patients aged 65 years and older will be included. Surgical wards of three hospitals will participate in the intervention groups; one surgical ward in another hospital will serve as a control group. The patients in the control group receive care as usual. A baseline measurement using a retrospective record review study will be conducted. In the following RCT the effects of three different interventions will be compared to usual care, randomisation is at patient level. Within the three intervention wards patients are randomly assigned to one of four intervention groups. The groups will receive the following interventions:

• Group 1: use of SBAR communication tool for nurses in the surgical wards

• Group 2: SBAR and patient safety card

• Group 3: SBAR and information leaflet (bundles) for after discharge

• Group 4: SBAR, patient safety card and information leaflet (bundles) for after discharge

During the study period the morning rounds will be observed once a month in each intervention ward to look at the information transfer and communication between care providers. Two weeks and six months after discharge patients will be interviewed about their recovery and the added value of the interventions. Six months after discharge the records of the included patients will be reviewed to detect possible adverse events and unintended harm. Figure 1 gives an overview of the inclusion and data collection.

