### Randomisation

In this study surgical wards in three different intervention hospitals and one surgical ward in a control hospital will participate. The eligible patients in the intervention wards will be randomly assigned to one of four intervention groups. Since the SBAR tool cannot be randomised on patient level due to practical reasons, this intervention will concern all patients in the intervention wards. Before the start of the inclusion all Informed Consent Forms and intervention materials will be assigned a unique study number. The study numbers are equally divided over four intervention groups, to ensure equal group sizes as much as possible. All materials for each individual number will be gathered and put into an envelope; the stack of envelopes will be kept in the ward in consecutive order of the study numbers. Each time an eligible patient can be asked to participate, the first envelope of the stack will be used. The process of randomisation is also shown in Figure 2.

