### Outcome measures

The primary outcome measures in this study are the incidence of complications and adverse events, mortality rate within six months after discharge and functional mobility six months after discharge. Secondary outcome measures are length of hospital stay, quality and completeness of information transfer and patient satisfaction with the instruments.

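### SBAR aims to improve the record from which complications and adverse events are counted, so event capture may differ in the non-randomised SBAR and programme contrasts

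*Protocol article*

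**What the plan says.** Under Intervention A, the Aim section includes the record itself: the tool is "for nurses to provide timely and accurate information during contacts with the physician and in the record keeping". The Implementation section describes the two-sided card: one side covers rounds and telephone consults, and for the reverse the text says "On the other side will be a description of the relevant topics for a structured and complete record keeping". Table 2, which shows the first side, also ends by telling the nurse to write the physician's comment and any change in the patient's state in the record.

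Exposure is by ward. Randomisation says of SBAR that "this intervention will concern all patients in the intervention wards", and Study design says "The patients in the control group receive care as usual". The baseline records date from 2007, before the intervention study began.

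Outcome measures states: "The primary outcome measures in this study are the incidence of complications and adverse events, mortality rate within six months after discharge and functional mobility" at six months. General data collection and follow up says that in the second record review "the reviewers will look for complications, adverse events, the quality of record keeping and written information for the transfers", and gives that review its purpose, for adverse events as well as complications: "This second record review study will be used to assess the effect of the complete intervention programme on the possible reduction in complications". The Method section of the baseline measurement lists the material reviewed as medical, nursing and (where they exist) outpatient records, and the second review uses identical methods. The Evaluation section for Intervention B also plans a comparison of event counts with the baseline.

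Strengths and limitations concedes that "The retrospective patient record review method relies exclusively on the information available in the hospital patient record" and that records can be incomplete. It presents this as a general weakness of the method and does not consider that the intervention may change completeness.

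**The concern.** An event can be counted only if it occurs and the reviewer can find it in the record. SBAR is intended to change the first and, through its charting component, may also change the second. The protocol expects record quality to respond, since it scores completeness in the same review as part of the SBAR evaluation, yet it reads the event counts as if capture were constant.

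If capture rises in the intervention wards, recorded events rise for that reason alone, against both the control ward and 2007. Adverse events have a second route: they count only at causation scores of 4 to 6, and fuller notes give the reviewer more to judge causation on. Blinding the reviewers limits judgement bias but cannot restore events that were never written down.

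At stake is the answer on SBAR (research question 2a) and on the programme as a whole. A real benefit could be understated or missed, and record review cannot later recover uncharted events.

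**Working it through.** **The plan's own figure.** Power calculation: 5-point reduction, SD 10, alpha 0.05, power 80%, 64 per group. The two-sided two-sample t-test gives 63.8, so 64 (normal approximation: 63), and 64 / 0.80 = 80. The figure reproduces. It treats the 5 points as the difference that will be seen, with no loss or distortion in capture. (Whether an SD of 10% suits a yes/no outcome is a separate question.)

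**Model.** Let p0 and p1 be the true complication risks under usual care and under the programme, with p1 = p0 − 0.05. Let s0 and s1 be the probabilities that a patient with a complication is identified from the record. False positives are ignored. Then:

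- recorded difference = p1·s1 − p0·s0
- the benefit vanishes when s1/s0 = p0/p1
- because s1 cannot exceed 1, reversal is possible only if s0 < p1/p0

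The protocol gives none of p0, s0 and s1. All are assumptions, shown over a range.

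| Control risk p0 | Programme risk p1 | Relative capture gain that cancels the effect (p0/p1 − 1) | Reversal possible only if s0 is below (p1/p0) |
|---|---|---|---|
| 20% | 15% | 0.05/0.15 = 33% | 75% |
| 30% | 25% | 0.05/0.25 = 20% | 83% |
| 40% | 35% | 0.05/0.35 = 14% | 88% |
| 50% | 45% | 0.05/0.45 = 11% | 90% |

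**Illustration at p0 = 40%, s0 = 80%.** Recorded control risk = 0.40 × 0.80 = 32.0%.

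| s1 | Recorded programme risk (0.35 × s1) | Recorded difference, points |
|---|---|---|
| 80% | 28.00% | −4.0 |
| 85% | 29.75% | −2.25 |
| 90% | 31.50% | −0.5 |
| 95% | 33.25% | +1.25 |
| 100% | 35.00% | +3.0 |

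**Illustration at p0 = 20%, s0 = 80%.** Recorded control risk = 0.20 × 0.80 = 16.0%. Even with perfect charting under SBAR, 0.15 × 1.00 = 15.0%, a difference of −1.0. The benefit is masked but not reversed.

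**Which contrasts are exposed**

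- Intervention wards against the control ward: exposed, since SBAR is on one side only.
- Intervention wards against 2007: exposed, for the same reason. This includes the baseline comparison under Intervention B, because card recipients also had SBAR.
- Card and leaflet contrasts among the four randomised groups: largely spared, since all four have SBAR.
- Mortality and six-month mobility: largely unaffected, since they do not depend on ward charting in this way.
- Events after discharge: less exposed, since the card acts on ward nurses.

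**The case against.** A good deal can be said for the plan.

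- **Capture outside the record exists.** A study questionnaire completed before discharge covers in-hospital delirium, falls, pressure wounds, and urinary and wound infections, which are the events most likely to depend on nursing notes. Included patients are also interviewed at two weeks and six months, the second time by an interviewer unaware of the group. This stands as a ready remedy, but it does not cure the plan as written: the programme effect is assigned to the record review, and the 2007 baseline has no such sources.
- **The definitions narrow the route.** A complication must call for a change of treatment or leave irreparable harm; an adverse event needs disability, death or a longer stay. Many such events would leave traces in medical notes or imaging whatever the nurses write. This limits the size of the bias without removing it.
- **The charting effect is not shown.** The content of the record-keeping side is not printed. Nurses are asked to use the card when consulting a physician or on rounds, with no explicit request to use it while charting. Implementation counts as successful at 60% of nurses.

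For this last reason, a reader who infers that unwritten events will in fact become written under SBAR, or that a null result would be an artefact of charting, goes beyond the document. It establishes a pathway, not its size.

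**Conclusion.** The concern holds for the non-randomised SBAR and programme contrasts on complications and adverse events. The intervention aims to improve the record, the record is the stated means of assessing the effect, and the comparators lack the intervention. If charting does improve, the bias runs against the programme.

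The size is unknown. Under the simple model, with assumed control risks of 20% to 50%, relative capture gains of 33% down to 11% cancel a true 5-point reduction. Masking needs less than that. Reversal needs more, and is possible only with baseline capture below about 75% at 20% risk or 88% at 40%.

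Two wider readings are not supported. One is that the primary results as a whole are compromised: mortality, six-month mobility and the randomised card and leaflet contrasts are largely outside this problem. The other is that all-event counts should give way to hard events such as reoperation or laboratory-confirmed infection. That would demote the delirium, falls and pressure ulcers that Intervention C sets out to reduce. Nor are such endpoints clearly immune, since the card prompts laboratory results and calls for the physician to come.

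**What to change.** Keep the all-complication and all-adverse-event outcomes. For the SBAR and programme contrasts:

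1. Add a tick-box to the review form for whether each event is evidenced outside the nursing notes, and prespecify a supporting analysis restricted to those events.
2. For the concurrent comparison with the control ward, also analyse complications from the pre-discharge questionnaire and the blinded six-month interview, both planned for all included patients. This cannot be done against 2007, and the interview reaches only patients who are alive and can be contacted.
3. Report event rates beside the completeness score already collected, by ward and period, with a sensitivity analysis over the capture ratio r = s1/s0. Under the model above, true risk ratio = recorded risk ratio / r. A range from below 1 up to at least 1.33 covers the break-even values shown.
4. State in advance that a difference in event rates in either direction, if accompanied by a difference in completeness, will not be taken as proof of benefit, of no effect or of harm. The rule must be symmetric, or it could be used to explain away real harm.

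The cost is protocol wording, one item on the review form, and a little more review and analysis work. The supporting analysis will rest on fewer events.
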